## Abstract

**Background:**

The strengthening or substitution of intravenous cytotoxic chemotherapy cycles by oral targeted anticancer therapies, such as protein kinase inhibitors (PKIs), has provided impressive clinical benefits and autonomy as well as a better quality of life for patients with cancer. Despite these advances, adverse event management at home and medication adherence remain challenging. In addition, PKI plasma concentrations vary significantly among patients with cancer receiving the same dosage, which could explain part of the observed variability in the therapeutic response.

**Objective:**

The aim of this optimizing oral targeted anticancer therapies (OpTAT) study is to optimize and individualize targeted anticancer treatments to improve patient care and self-monitoring through an interprofessional medication adherence program (IMAP) combined with measurement PKI plasma concentrations.

**Methods:**

The OpTAT study has two parts: (1) a 1:1 randomized medication adherence program, in which the intervention consists of regular motivational interviewing sessions between the patient and the pharmacist, along with the delivery of PKIs in electronic monitors, and (2) a systematic collection of blood samples and clinical and biological data for combined pharmacokinetic and pharmacodynamic analysis. On the basis of the electronic monitor data, medication adherence will be compared between groups following the three operational definitions: implementation of treatment during the persistent period, persistence with treatment and longitudinal adherence. The implementation will be described using generalized estimating equation models. The persistence of PKI use will be represented using a Kaplan-Meier survival curve. Longitudinal adherence is defined as the product of persistence and implementation. PKI pharmacokinetics will be studied using a population approach. The relationship between drug exposure and efficacy outcomes will be explored using Cox regression analysis of progression-free survival. The relationship between drug exposure and toxicity will be analyzed using a pharmacokinetic-pharmacodynamic model and by logistic regression analysis. Receiver operating characteristic analyses will be applied to evaluate the best exposure threshold associated with clinical benefits.

**Results:**

The first patient was included in May 2015. As of June 2021, 262 patients had participated in at least one part of the study: 250 patients gave at least one blood sample, and 130 participated in the adherence study. Data collection is in process, and the final data analysis is planned to be performed in 2022.

**Conclusions:**

The OpTAT study will inform us about the effectiveness of the IMAP program in patients with solid cancers treated with PKIs. It will also shed light on PKI pharmacokinetic and pharmacodynamic properties, with the aim of learning how to adapt the PKI dosage at the individual patient level to increase PKI clinical suitability. The IMAP program will enable interprofessional teams to learn about patients’ needs and to consider their concerns about their PKI self-management, considering the patient as an active partner.

**Trial Registration:**

ClinicalTrials.gov NCT04484064; https://clinicaltrials.gov/ct2/show/NCT04484064.

**International Registered Report Identifier (IRRID):**

DERR1-10.2196/30090

## Introduction

### Background

On the basis of the Global Cancer Observatory estimates, cancer was responsible for almost 10 million deaths globally in 2020 [1], making it a leading cause of death [2]. In Switzerland, more than 40,000 new patients are diagnosed with cancer each year [3]; however, the mortality rate of many cancers is decreasing, mainly because of the implementation of both screening programs and novel targeted and immune-related therapies [4].

For 15 years, the strengthening or alternatively the substitution of intravenous cytotoxic chemotherapy cycles by oral, sometimes long-term, targeted anticancer therapies has offered impressive clinical benefit and autonomy as well as a better quality of life for patients with cancer. Targeted cancer therapies involve protein kinase inhibitors (PKIs) and inhibitors of growth factor receptors, which are used to treat a variety of cancers, including gastrointestinal stromal tumors; kidney, thyroid, colorectal, lung, and breast cancers; melanoma; and sarcomas. Although treatment failure and poor tolerance are common in clinical practice, they cannot all be attributed to solid tumor multidrug resistance, as they can also be triggered by suboptimal medication adherence or inadequate drug plasma concentrations.

Suboptimal medication adherence is one of the causes of cancer progression and higher costs for health systems [5-7]. Thus, supporting patient drug self-management is key to achieving the best clinical outcome. In the past decade, interventional studies have focused mainly on patients with breast cancer treated with hormonal treatments and patients with chronic myeloid leukemia using imatinib. Evaluations of interventions to support PKI adherence in other solid cancers are scarce. In a systematic review, adherence to oral anticancer therapies was estimated to vary between 46% and 100% [8]. This review addressed adherence to various classes of oral anticancer therapies using various measures of adherence among patients with solid cancers, multiple myeloma, and chronic leukemia. Adherence estimation is not often reliable, as it is frequently evaluated through a moderate-quality methodology using subjective self-report questionnaires [9-11]. The link between longitudinal medication adherence, clinical factors, quality of life, survival, and cancer progression has been underinvestigated in the literature [12].

Since 1995, a routine interprofessional medication adherence program (IMAP) has been implemented at the University Community Pharmacy of the Center for Primary Care and Public Health Unisanté (Lausanne, Switzerland) to support drug self-management in patients with chronic illness [13]. Before initiating the optimizing oral targeted anticancer therapies (OpTAT) study, we conducted a feasibility study in which the included patients were mostly diagnosed with gastrointestinal stromal tumors or breast cancer. Adherence was estimated for several classes of oral anticancer therapies (capecitabine, letrozole, exemestane, imatinib, sunitinib, and temozolomide). We showed that patients with cancer agreed to participate and adopted the program; 12-month persistence was estimated at 85%, and the 12-month implementation rate was 97% in persistent patients [14].

Oral PKIs are licensed at a fixed dose despite the variable plasma concentrations observed in real-life situations [15,16]. This substantial interpatient pharmacokinetic variability may be explained by demographic (eg, age, body weight, and sex) and environmental factors (eg, concomitant medication and smoking), relevant physiopathological conditions (eg, organ failure and albumin levels) [17,18], genetic polymorphisms of metabolic enzymes or drug transporters, and patient behavior (eg, medication adherence) [12]. The characterization of pharmacokinetic variability is essential in oncology, given the risk of under- or overexposure, which may contribute to insufficient efficacy or undesirable toxicity in patients with cancer, respectively. Moreover, considerable efforts remain to be undertaken to characterize the correlation between drug plasma concentrations and the therapeutic response of most PKIs and to define the therapeutic targets associated with clinical benefits in the context of therapeutic drug monitoring [19].

### Objectives

The global aims of the OpTAT study are to establish the necessary knowledge to build rational monitoring strategies through medication adherence monitoring and patient-adjusted dosage in real-life conditions, which should contribute to optimizing the therapeutic benefit of PKIs, in order to improve outpatient cancer care.

The primary objectives are to better characterize the prospective and longitudinal patterns of PKI adherence in patients participating in a medication adherence program versus a control group and to identify key driver-modifiable adherence factors.

The secondary objectives are to quantify interpatient variability, identify sources of variability in serum PKI levels, and characterize the relationships between the serum concentration, the therapeutic response and the toxicity of these treatments in a population of patients with solid cancer.

The hypothesis states that the medication adherence program will increase PKI implementation and persistence before the treatment is stopped for any reasons beyond the patient’s control or therapeutic change compared with the control group. Moreover, it is hypothesized that interpatient variability in PKI plasma concentrations plays a fundamental role in the heterogeneity of the therapeutic response and may play a role in PKI adherence.

## Methods

### Ethical Considerations

The local ethics committee (Vaud, Switzerland) approved the OpTAT study in April 2015. Since then, two amendments have been accepted in July 2017 and October 2020. The study will be conducted in accordance with the current version of the Declaration of Helsinki and international good clinical practice principles. The protocol was peer-reviewed by five experts in April 2017 (Multimedia Appendix 1), leading to the founding of the study by the Swiss Cancer Research Foundation. This protocol was written according to the SPIRIT (Standard Protocol Items: Recommendations for Interventional Trials) guidelines (Multimedia Appendix 2) [20].

### Trial Design

This monocentric prospective study comprises two parts: (1) an open randomized controlled medication adherence study and (2) an observational pharmacokinetic and pharmacodynamic study. This design (Figure 1) explores whether medication adherence evolves differently in each group and explores the interplay between adherence and PKI pharmacokinetic parameters.

**Figure 1 figure1:**
[figure not shown]
Design of the optimizing oral targeted anticancer therapies study. BMQ: Belief about Medicines Questionnaire; EORTC-QLQ: European Organization for Research and Treatment of Cancer Quality of Life Questionnaire; SatMed: Treatment Satisfaction with Medicines Questionnaire.

### Enrollment of Participants

This translational study will be conducted at the Medical Oncology Service of the Department of Oncology of the Lausanne University Hospital (CHUV) outpatient clinic (Lausanne, Switzerland) in collaboration with the Community Pharmacy of the Center for Primary Care and Public Health Unisanté (Lausanne, Switzerland) and the Center for Research and Innovation in Clinical Pharmacy Sciences (CHUV).

Adult patients aged >18 years who were treated with a PKI for solid tumors and followed at the CHUV were eligible to participate in this study. Participants with an inability to make decisions, with cognitive disorders, under tutelage, or not fluent in French or English or without the aid of an interpreter will be excluded from the study. Patients will be excluded solely from the medication adherence part of the study if they do not self-manage oral anticancer treatment (ie, nursing homes and home care services) or if they are already enrolled in an interventional study. If one PKI is switched to another PKI during the study, the patient will continue to participate in the study. However, if the PKI treatment is stopped or changed to a non-PKI anticancer treatment, the participant exits the OpTAT study; but, the data collected are kept for analysis.

The OpTAT study is voluntary, and patients will need to sign an informed consent form to participate in the medication adherence study, the pharmacokinetic and pharmacodynamic study, or both. The recruitment of participants began in May 2015. It ended in March 2021 for the medication adherence part but is ongoing until December 2021 for the pharmacokinetics part.

Oncologists were asked to refer eligible patients to a pharmacist PhD student or to the research staff from the Center of Experimental Therapeutics (CHUV), who will present the informed consent form to the patient after the medical visit. The participants will follow their treatment as usual, and no changes in the usual medical procedure will be made. No payment or compensation will be provided to the patients or to the oncologists as the patients are being seen as part of their routine follow-up clinical care.

### Randomized Controlled Medication Adherence Study

#### Instruments: Use of the Electronic Monitors MEMS and Questionnaires in Both Groups

All patients participating in the medication adherence study will use an electronic monitor (MEMS and MEMS AS, AARDEX Group) for 12 months or until PKI is stopped. The electronic monitor registers the date and time of each opening, and a liquid-crystal display monitor on top of the cap indicates the number of daily openings to the patient. All patients included in the study will be asked to complete two validated questionnaires at three timepoints: inclusion, 6 months postinclusion, and at the end of the study. The first questionnaire is the *Belief about Medicines Questionnaire*, which assesses the patient’s cognitive representation of medication [21]. The second is the *European Organization for Research and Treatment of Cancer Quality of Life Questionnaire* (version 3.0), which assesses the quality of life of patients with cancer [22]. During the initial months of the study implementation, the patients with cancer filled out the *Treatment Satisfaction with Medicines Questionnaire* [23]; however, it was switched to the *European Organization for Research and Treatment of Cancer Quality of Life Questionnaire*, as the latter was more adapted to patients treated with a PKI. The questionnaires were translated and validated in French, with satisfactory psychometric properties [24-26].

#### Repeated Medication Adherence Interviews and Feedback (Intervention Group)

Patients included in the intervention group will visit the routine IMAP of the pharmacy of Unisanté. They will attend 15- to 30-minute medication adherence interviews, which will take place after each clinical appointment over 12 months. On the basis of the information-motivation-behavior model embedded in sociocognitive theory [27], the pharmacist will explore in depth the home drug self-management skills, side effect management, motivation, self-efficacy, and consider cofactors such as depression, anxiety, and drug or alcohol addiction. Patients’ beliefs about PKIs will be explored, and information about the PKI will be delivered and discussed at each visit. Determinants of and gaps in medication adherence will be discussed with the pharmacist in an empathetic and nonjudgmental way using motivational interviewing skills.

The electronic monitor data will be uploaded to MEDAMIGO software (MEMS and MEMS AS), which generates graphs of electronic monitor daily openings. Feedback on adherence to PKI therapy, based on the information generated by the electronic monitor, will be provided to and discussed with the patient. Interprofessionality is a cornerstone of the program, and pharmacists will summarize the intervention in a semistructured report sent to the oncologist after each intervention. During the COVID-19 pandemic, motivational interviews will be conducted by phone calls with patients considered by clinicians to be at a high risk of SARS-CoV-2 infection. All pharmacists who perform the medication adherence intervention must have attended specific training to lead motivational interviews (two full-day medication adherence initial training and continuous education based on the debriefing of a motivational interview with a patient every 12-18 months) [13].

#### Control Group

Patients included in the control group will use an electronic monitor but will be considered standard-of-care patients as they will not receive any medication adherence intervention. The electronic monitor opening data of the control group will be concealed from the patients, pharmacy team, clinicians, and investigators until the end of the study. If an oncologist expressively asks for adherence data because of stringent and urgent clinical matters, the patient will be excluded from the OpTAT study and referred to the routine medication adherence program of the Community Pharmacy of the Center for Primary Care and Public Health Unisanté.

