#### Assignment of the Intervention

The collection of adherence data patterns in both groups at baseline is crucial to check whether adherence patterns are homogeneous between the groups before the intervention starts. In both groups, patients will use an electronic monitor for at least 21 days before randomization. At the end of the baseline period, the patients will be randomized 1:1 to either attend the medication adherence program (intervention group) or be part of the standard of care (control group; Figure 1). The randomization lists will stratify participants according to their cancer type and the time elapsed between PKI initiation and the time of inclusion (less or more than 30 days). The randomization sheet lists 1 (intervention group) or 0 (control group) and will be provided by an independent researcher from the Unisanté Research Support Unit. The randomization list established by Excel (version 2016, Microsoft) will be based on variable size block randomization to prevent predictability and ensure a balanced allocation to each group. After randomization, the patient, research team, pharmacy, and clinical team will all be aware of the assigned group.

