### Outcomes

#### Primary Outcomes: Randomized Controlled Medication Adherence Study

The primary outcome was global adherence, defined as the percentage of days with correct medication use of each subject. The sample size was calculated to ensure sufficient power to test the difference in the mean logit global adherence between groups (see the *Sample Size* section). Medication adherence will also be compared between groups following the three operational definitions defined by the EMERGE (European Society for Patient Adherence, Compliance, and Persistence Medication Adherence Reporting Guideline) guidelines: implementation of treatment during the persistent period (daily management of oral targeted anticancer drugs), persistence with treatment (the distribution of times between enrollment and discontinuation), and longitudinal adherence (the product of persistence and implementation) [14,28,29].

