Sociodemographic data and quality of life and beliefs about medication of patients who refused to participate and completed both questionnaires versus those who accepted to participate in the adherence study will be compared at baseline. For patients included in the adherence study, the results of the questionnaires will be compared at randomization, 6 months, and at the end of the study. Changes in *Belief about Medicines Questionnaire* and *European Organization for Research and Treatment of Cancer Quality of Life Questionnaire* or the *Treatment Satisfaction with Medicines Questionnaire* will be described longitudinally for the included patients and transversely per group at 6 and 12 months. Medians and IQRs or proportions will be used as appropriate. Nonparametric tests (eg, Mann-Whitney-Wilcoxon) or Fisher exact test of two proportions will be used to test the differences between groups.

Ultimately, the adherence patterns and their relationship with drug exposure and clinical response will be evaluated in an exploratory analysis.

To minimize interpretation bias, the statistician will not be aware of the group assignments during the analysis. The data will be analyzed in an intention-to-treat manner. All statistical analyses will be performed using the R statistical package (version 3.6, The R Foundation for Statistical Computing) [36].

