#### Missing Data

Missing data will not be imputed but will be clearly identified and considered during the analysis process (nature and frequency) and described in the publication.

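### Control patients whose oncologist requests adherence data are excluded after randomization, a one-arm rule not reconciled with the intention-to-treat analysis and without a statement that their data are kept

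*Protocol article*

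**What the plan says.** The Control Group section conceals the monitor data of controls until the end of the study and then makes an exception. It begins "If an oncologist expressively asks for adherence data because of stringent and urgent clinical matters" and continues that "the patient will be excluded from the OpTAT study and referred to the routine medication adherence program". The section on repeated interviews and feedback identifies that routine program as the trial's own intervention. It also says that, for intervention patients, "pharmacists will summarize the intervention in a semistructured report sent to the oncologist after each intervention".

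Under Assignment of the Intervention the trial is open: "After randomization, the patient, research team, pharmacy, and clinical team will all be aware of the assigned group".

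On analysis, the Medication Adherence Analysis section states: "The data will be analyzed in an intention-to-treat manner". The Missing Data section adds: "Missing data will not be imputed". The primary outcome section reads: "The primary outcome was global adherence, defined as the percentage of days with correct medication use of each subject".

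For a different kind of exit, when the protein kinase inhibitor is stopped or replaced by another class of anticancer drug, Enrollment of Participants says that "the participant exits the OpTAT study; but, the data collected are kept for analysis". The Control Group section has no matching provision.

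**The concern.** The rule acts after randomization, can act in one arm only, and is set off by clinicians who know the arm. The trigger is a request for adherence data and the response is referral to an adherence program, so the patients affected are plausibly those thought to be taking their drug poorly. That links the exclusion to the primary outcome.

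If excluded is taken at face value and these patients leave the analysis, the remaining controls look more adherent than the randomized control group was. The difference between arms then shrinks and power falls. No imputation is planned that could restore what is lost. The sample size section allows for 10% dropout at mid-year but not for selective loss from one arm.

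**Working it through.** **Step 1. Can the rule operate in both arms?** No. It stands under Control Group only. Intervention-arm oncologists receive a report after each session, so they have no need to make the request, and no exclusion follows when they learn about adherence.

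**Step 2. Is it reconciled with intention-to-treat?** No. The two statements are compatible if exclusion only ends follow-up and the patient is still analyzed as a control. They conflict if the patient leaves the analysis set. The protocol shows in the enrollment section how it words an exit with data retained, and it does not use that wording here.

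**Step 3. Reproduce the planned sample size.** Inputs from the Sample Size section: intervention stable at 95%; control falling from 95% to 80% over 340 days; SD 1.8 on the logit scale; 10% dropout at mid-year; two-sided t test at 0.05; 60 per group; 80% power.

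- Stated individual ranges: logit(0.80) ± 1.96 × 1.8 gives 10.5% to 99.3%, and logit(0.95) ± 1.96 × 1.8 gives 35.8% to 99.85%. Both agree with the protocol.
- With the control decline linear on the percentage scale, the mean over follow-up of logit(0.95) − logit(0.95 − 0.15t), for t from 0 to 1, is 0.931.
- Patients per arm = 2 × (1.960 + 0.842)² × 1.8² / 0.931² = 58.7, so 59. Power at 60 per arm is 80.9%.
- Simulation of 340 daily binary values per patient, with 10% stopping at day 170 and global adherence taken over the days observed (3,000 replicates): mean logit difference 0.92, power 80.6%.

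The planned figure reproduces. A decline linear on the logit scale would give a difference of 0.779 and 66% power, which does not match, so the percentage-scale reading is used below.

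**Step 4. Apply the exclusion rule.** The protocol does not give the share of controls excluded, so 5% (3 of 60) and 10% (6 of 60) are assumptions. Each control gets a score, r × (standardized observed logit adherence) + √(1 − r²) × standard normal noise, and the lowest scores are excluded. Thus r = 0 means that requests are unrelated to adherence, and r = 1 means that exactly the worst adherers are queried. Each cell shows the mean logit difference and power from 1,500 replicates (simulation error of power about 1 percentage point).

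| Controls excluded | r | All their data dropped | First 120 days kept (assumed) |
|---|---|---|---|
| 5% | 0 | 0.93, 80% | 0.90, 79% |
| 5% | 0.5 | 0.81, 71% | 0.90, 80% |
| 5% | 1 | 0.73, 64% | 0.88, 78% |
| 10% | 0 | 0.91, 78% | 0.87, 76% |
| 10% | 0.5 | 0.75, 63% | 0.87, 76% |
| 10% | 1 | 0.59, 48% | 0.89, 79% |

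A separate run with exclusion at day 170 and data kept gave a difference of 0.88 to 0.90 and power of 78% to 80% for 3 of 60, and 0.88 to 0.89 and 79% for 6 of 60. Without exclusion the same run gave 0.90 and 79%.

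Retaining the data up to referral therefore removes most of the loss. A small shrinkage remains because the retained days come from the early period, before control adherence has fallen far.

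**The case against.** The strongest reply is that the protocol nowhere says the data are deleted. Exclusion may mean only that follow-up ends. With intention-to-treat promised, and data retained for another type of exit, the sections can be read together without conflict, and a condensed article may leave the analysis set to the full protocol or analysis plan. This stands in part. A reader might infer that the plan discards these patients' data, but the text does not say so. What remains is that the article states the exclusion explicitly, applies it to one arm, and omits the retention clause that it uses elsewhere.

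Second, a reader might infer that every request signals suspected non-adherence, so that bias toward zero is certain. The stated trigger is only an urgent clinical matter, which could be unexplained toxicity. If requests are unrelated to adherence, the bias is about nil and the cost is a little power.

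Third, a reader might take the 64% and 48% as the expected loss. They require dropping all data of the worst controls, ranked on full-year monitor data that are concealed from clinicians and not yet complete when a request is made. They are an outer bound. The wording of the trigger also suggests a rare event, so the loss could be trivial.

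Fourth, if the inferred direction is right, the bias is conservative and would not create a false claim of benefit. That is fair. It lowers the urgency but does not settle who belongs in the primary analysis.

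**Conclusion.** The concern holds as an unreconciled conflict between the Control Group rule and the intention-to-treat statement. The exclusion is post-randomization, possible in one arm only, triggered by clinicians who know the allocation, and plausibly related to the primary outcome.

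Its size depends on three things that the protocol does not give: how many controls are excluded, how closely requests track poor adherence, and whether data before referral are kept. If 5% to 10% are excluded and their data dropped, power falls from about 80% to 71% or 63% at a moderate correlation (0.5), and to 64% or 48% in the extreme case. It stays at about 76% to 80% if data up to referral are kept with 10% excluded, or if requests are unrelated to adherence.

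The documents do not support saying that the plan deletes suspected poor adherers, or that a large bias toward zero will occur. They support saying that the rule as written permits it.

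**What to change.** Reconcile the two sections. State that a control patient referred under this rule stays in the control arm of the intention-to-treat set, with monitor data up to referral kept in the primary analysis. Report the number of such patients and the dates of disclosure.

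Openings recorded after referral need care. The patient is by then in the program that is the trial's intervention, so counting those days as control time dilutes the contrast, and nothing in the protocol says that they remain study data. Use them only where they are available and covered by consent, as a treatment-policy sensitivity analysis labelled with that limitation.

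The referral pathway itself does not change. The cost is a sentence or two in the Control Group and analysis sections and a short line in the report. The protocol places the final analysis in 2022, after recruitment to the adherence part ended, so the analysis set could still be fixed before the data are analyzed.
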